**Methods:**

This is a single-blinded, pragmatic, cluster randomised controlled trial. Ten subacute hospital sites (i.e. clusters) across Australia will be allocated 1:1, stratified by state to a multi-component intervention comprising a training programme for health providers, implementation of a screening tool and use of site champions, or no additional training or support. Outcomes will be collected at baseline, 4 and 9 months. Our co-primary outcomes are change in health providers’ knowledge of responding to elder abuse and older people’s sense of safety and quality of life. We will include all inpatients at participating sites, aged 65 + (or aged 50 + if Aboriginal or Torres Strait Islander), who are able to provide informed consent and all unit staff who provide direct care to older people; a sample size of at least 92 health providers and 612 older people will provide sufficient power for primary analyses.

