### Sample size

As health providers are not anticipated to be systemically different based on location (clusters), we have not accounted for ICC for health providers; therefore, we calculated that 60 health providers would be sufficient to detect a medium effect (Cohen’s *d* of 0.5) on the KAMA at a power of 80% and a significance level of 1%. This difference is similar to that reported in our previous research, and the sample size calculation uses a standard deviation of 4.8 as previously reported [34]. We calculated that we need 10 clusters (5 intervention, 5 control) with 40 older people in each cluster to detect a medium effect on the ASCOT at a power of 80% and a significance level of 5%. As responses to elder abuse vary across jurisdictions, an ICC of 0.1 is assumed for older people with the standard deviation of 0.2 reported by others [35], calculated using the Shiny Calculator for Sample size for Cluster Randomised Trials [36]. Assuming 53% refusal rate to participate/unable to consent as observed in our group’s prior work in the UK [37, 38], the total sample size is 92 health providers and 612 older people (~ 60 older people/site).

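### The totals of 92 health providers and 612 older people do not follow from the stated 53% refusal rate: the plan multiplied by 1.53 where it should have divided by 0.47

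*Protocol article*

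**What the plan says.** The Sample size section of the protocol article builds its totals in two steps.

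- **Health providers:** "we calculated that 60 health providers would be sufficient to detect a medium effect". The calculation takes d = 0.5 for the KAMA, with 80% power at the 1% level, and makes no allowance for clustering.
- **Older people:** "we need 10 clusters (5 intervention, 5 control) with 40 older people in each cluster", that is 400. The target here is a medium ASCOT effect, with 80% power at the 5% level and an ICC of 0.1.

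One allowance, taken from the group's earlier UK studies, is then applied to both groups: "Assuming 53% refusal rate to participate/unable to consent". The outcome of this step is given as follows: "the total sample size is 92 health providers and 612 older people (~ 60 older people/site").

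The abstract (Methods) carries the same totals as a guarantee of power: "a sample size of at least 92 health providers and 612 older people will provide sufficient power for primary analyses". The primary hypotheses concern 4 months (Aims and hypotheses), and follow-up runs to 9 months (Outcome assessments).

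**The concern.** A rate of refusal or inability to consent describes what happens before enrolment. It determines how many people must be approached to obtain a given number of participants. If 53% do not take part, 47% do, and the required number is divided by 0.47. The stated totals are too small for that.

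The text also leaves open whether 92 and 612 are people to approach or people to enrol. On the first reading the trial would enrol fewer than its own calculation requires. On the second, the reason given for the increase is not the one that matters, because people who refused were never going to be counted among those enrolled. Either way, the recruitment target and its stated basis do not match, and a site cannot tell from this section whether about 60 older people is a number to invite or to enrol.

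**Working it through.** **Inputs** (Sample size section): base numbers 60 and 10 × 40 = 400; non-participation rate 0.53; stated totals 92 and 612; ICC 0.1; 5 clusters per arm. Cohen's d = 0.5 is stated for the KAMA. For the ASCOT the text says only that the effect is medium, so d = 0.5 is an assumption there. The 1% level is taken as two-sided, which the text does not say.

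**1. Reproducing the plan's totals, n × (1 + 0.53)**

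- 60 × 1.53 = 91.8, rounded up to 92
- 400 × 1.53 = 612.0

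Both match, so this is the operation used.

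**2. The operation that the stated rate requires, n / (1 − 0.53)**

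- 60 / 0.47 = 127.7, rounded up to 128
- 400 / 0.47 = 851.1, rounded up to 852 (about 85 per site)

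**3. If 92 and 612 are people approached**

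- 92 × 0.47 = 43.2 providers; 1 − 43.2/60 = 28% short
- 612 × 0.47 = 287.6 older people, about 29 per site instead of 40; 1 − 287.6/400 = 28% short

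**4. If 92 and 612 are people enrolled**

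The loss after enrolment that still leaves the base numbers is:

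- 1 − 60/92 = 34.8%
- 1 − 400/612 = 34.6%

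To enrol these numbers at 53% non-participation, the trial would have to approach 92/0.47 = 195.7 (196) providers and 612/0.47 = 1302.1 (1303) older people.

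**5. Power cost of this error alone (approached reading, d = 0.5)**

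ASCOT, with m people per cluster: design effect = 1 + (m − 1) × 0.1; noncentrality = 0.5 / √(2 × design effect / (5m)); 5% two-sided.

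| m | Design effect | Noncentrality | Power, normal approximation | Power, t on 8 df |
|---|---|---|---|---|
| 40 | 4.90 | 2.26 | 62% | 51% |
| 28.76 | 3.78 | 2.18 | 59% | 48% |

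KAMA, two-sample t-test with no clustering, 1% two-sided: noncentrality = 0.5 × √(n per arm / 2).

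| Total n | Noncentrality | Power |
|---|---|---|
| 60 | 1.94 | 24% |
| 43 | 1.64 | 16% |

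The error therefore costs about 3 percentage points for the ASCOT and 8 to 9 for the KAMA. The starting values of 62% (or 51%) and 24% are already below the stated 80%. That gap belongs to the base figures and would remain after the inflation is corrected.

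**The case against.** The strongest reply is that 92 and 612 are enrolment targets. The Sample size section calls them the total sample size and gives about 60 older people per site, and the abstract says that they provide power, which nobody would say of a number of invitations. On that reading the trial enrols more than 60 and 400 and has about 35% to spare. This stands, and it removes any certain shortfall. It does not rescue the calculation, because the margin is then justified by a rate that does not act on enrolled people.

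A reader might infer that the error takes power from 80% down to 59% for the ASCOT and 16% for the KAMA. The documents do not support this. The fall starts from about 62% and 24% and applies only to the approached reading. For older people the ten clusters and the ICC of 0.1 dominate: even 85 per cluster gives only about 66% by the normal approximation.

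A reader might also infer that the plan has no allowance for attrition. The article condenses a fuller protocol (version 3, under Trial status) that is not shown and may give a rate, so the absence of one here is not a fault. Likewise, one might object that inability to consent hardly applies to staff. Refusal does apply to them, however, and whether 53% suits them depends on cited work that is not at hand.

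**Conclusion.** The point holds as an error of arithmetic and labelling. The totals of 92 and 612 are reproduced only by multiplying by 1.53, whereas the stated 53% rate gives 128 and 852. This rests on the article's own figures and needs no further assumption.

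The consequence depends on a reading that the text does not settle. As people approached, 92 and 612 fall 28% short of the required numbers, at the modest power cost shown above. As people enrolled, which the wording favours, there is no shortfall, but the margin of about 35% carries the wrong justification. It should be fixed. It does not by itself threaten the trial, and correcting it will not bring power to 80%.

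**What to change.** State in the Sample size section whether 92 and 612 are people approached or people enrolled, and align the abstract.

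- **If enrolled:** keep 92 and 612, remove refusal as their justification, and state that they allow about 35% loss by 4 months. Give the numbers to approach at 53% non-participation separately, as 196 providers and 1303 older people.
- **If approached:** either restate the expected yield as about 43 and 288, or correct the numbers to approach to at least 128 and 852. Note that 128 and 852 yield only the base 60 and 400 and leave no margin for loss to follow-up.

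On the enrolled reading the cost is protocol wording and screening-log targets, with no change to planned enrolment. On the approached reading, correcting the numbers means inviting at least 36 more providers (128 − 92) and 240 more older people (852 − 612). Recruitment has commenced and is expected to end in August 2025 (Trial status), so the clarification should reach the sites while it can still guide recruitment.

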### Recruitment

Site champions will recruit health providers and older people in intervention and control arms. They will promote the study to subacute staff, during staff meetings, through posters and emails targeting relevant staff. A QR code will link to further information about the study. For the 4- and 9-month follow-up, site champions will remind staff up to 3 times verbally or by email.

Site champions will prospectively recruit all older patients who meet eligibility criteria, as identified through staff meetings, medical files, and discussion with patients. They will provide each eligible participant with an invitation letter and PICF. Older people can choose to complete paper-based surveys with a reply-paid envelope provided or a text message or email link with the necessary information, as we have successfully used in prior research [39]. Older people will be recruited once the health providers in the intervention arm have completed the training and use of the screening tool has been implemented at the site; therefore, the baseline, 4-month, and 9-month time points for older people will be slightly later.

Based on stakeholder consensus, we aim for 60% of eligible staff to complete the training prior to commencing the implementation of the screening tool to maximise patient exposure. It is possible that an older adult participant in the intervention arm will receive clinical care from someone who has not completed the training. Thus, we will also capture the ‘dose’ for each site as a percentage of eligible staff who have completed the training.

### Group allocation

Stratified randomisation will allocate clusters (subacute sites) to either intervention or wait list control using a minimisation procedure. State (VIC, NSW, SA, WA) is a stratification factor. This is a single-blinded study where the statistician and outcome assessors will be blinded to allocation. Randomisation will occur following completion of baseline data collection for health providers. An independent biostatistician who is not a member of the research team will generate the allocation sequence. It is not possible to blind participants to group allocation when collecting the post-intervention scores. During the assessment period, we will ask health provider participants not to discuss the study outside their site.

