### Control

The control arm will be waitlisted and given access to the training after 9 months. Control arm sites will also recruit site champions, who will be trained and supported in data collection. They will encourage completion of the outcome measures for health providers, recruit older people and collect data, and collect deidentified site data but will not provide further input beyond their normal clinical role.

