#### Health providers

Health providers will complete a demographic survey (age, gender, profession, years of experience in profession, and whether they have completed elder abuse training prior to the trial). They will also complete the adapted Knowledge and Management of Abuse (KAMA) [27] (primary outcome) adapted for an Australian subacute care setting, the Australian adaptation of the Caregiver Scenario Questionnaire (CSQ) [28, 29], and Carolina Opinions on Care of Older Adults (COCOA) survey [30] (secondary outcomes) via online survey in REDCap.

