#### Older people

Older people will complete a demographic survey (age, gender, education, postcode, country of birth, language/s spoken, English language skills, First Nations status, reason for admission and underlying health risk factors for elder abuse (e.g. dementia, mobility), the Adult Social Care Outcomes Toolkit (ASCOT) [31] (primary outcome), the Short Form Survey-12 (SF-12v2) [32], and an adapted Resource Utilisation in Dementia lite (a-RUD-lite) (secondary outcomes) via online/paper/telephone survey. Site champions will support older people where required and record the older person’s length of admission once discharged.

**Table 1 Tab1:** Procedure timeline

**Procedures**	**Assessment/procedure**	**Screening**	**Baseline**	**4-month follow-up**	**9-month follow-up**

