### Limitations

We will exclude patients who receive subacute care at home, despite this being an increasingly popular model of care. This minimises the risk of screening in the presence of a perpetrator, which would reduce the likelihood of disclosing abuse and may pose risks to the older person and/or care staff.

Second, we will exclude older adults without the capacity to consent to research participation to avoid seeking proxy consent from a substitute decision maker, which could include a perpetrator of abuse.

Finally, the recruitment of older people by site champions after randomisation introduces a risk of bias as site champions will know whether they are in the intervention or control arm. This common problem with cluster RCTs will be managed in the analytic strategy (e.g. through difference-in-differences techniques).

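### The protocol claims blinded outcome assessors but describes none for either co-primary outcome, and the helpers and record abstractors it names know their arm

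*Protocol article*

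**What the plan says.** The Group allocation section describes the study as single-blinded and states that "the statistician and outcome assessors will be blinded to allocation". The abstract also calls the trial single-blinded. Later in the same section comes a concession: "It is not possible to blind participants to group allocation when collecting the post-intervention scores".

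Under Outcome assessments, the adapted KAMA (health providers' primary outcome) is completed by the providers in an online survey. The ASCOT (older people's primary outcome) is completed by the older person online, on paper or by telephone, and "Site champions will support older people where required". The Control section says that champions at control sites will "recruit older people and collect data". The Sites subsection has champions go through medical records for abuse cases and referrals. Data collection and management has them check older people's responses for clinical concerns. Of the champions' own blinding, Limitations says that "site champions will know whether they are in the intervention or control arm".

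**The concern.** A statement that outcome assessors are blinded tells readers, and anyone rating risk of bias, that the person producing the score did not know the arm. For a self-completed questionnaire the respondent is in effect the assessor, and here the respondent is unblinded at follow-up. Where an older person needs help, the named helper is the site champion, who knows the arm. In the intervention arm, this is also the person promoting the training and the screening tool.

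The ASCOT asks for subjective judgements, so help from someone invested in the intervention could move answers differently by arm. A larger sample does not remove such a bias. What is at stake is what the trial may claim about protection from detection and response bias.

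**Working it through.** The core of the point is a comparison of sections.

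| Outcome | Who gives or handles it | Knows the arm? |
|---|---|---|
| KAMA, baseline | Provider, online | No: completed before randomisation (Outcome assessments; Group allocation) |
| KAMA, 4 and 9 months | Provider, online | Yes, by the concession in Group allocation |
| ASCOT, self-completed | Older person | Not blindable at post-intervention assessments (Group allocation) |
| ASCOT, where help is needed | Site champion supports | Champion knows (Limitations) |
| ASCOT, telephone | Caller not stated | Not stated |
| Detection and referral data | Site champion abstracts from records | Champion knows, once the site is randomised |
| Data entry | Research team | Not stated |

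Three observations follow.

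1. No row names a blinded assessor. The primary hypothesis concerns 4 months (Aims and hypotheses), and there both scores come from unblinded respondents.
2. Older people are recruited after randomisation, once training is done and the screening tool is in use (Recruitment). Their baseline ASCOT is therefore also taken when the champion knows the arm. The difference-in-differences technique mentioned in Limitations has no pre-allocation ASCOT to work from. It would remove a shift that is equal at baseline and follow-up, but nothing in the article ensures that assistance is equal at the two times.
3. Limitations raises champions' knowledge only in connection with recruiting older people, and does not reconcile it with the assessor-blinding statement.

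**Size, as illustration only.** The plan states no figure for this bias, so there is none to reproduce.

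Inputs:
- ASCOT SD of 0.2 (Sample size).
- A medium effect, taken as 0.5 SD. The article gives that value for the KAMA; applying it to the ASCOT is an assumption.
- A shift of 0.1 to 0.2 SD in assisted surveys, in one arm only. This is an assumption with no basis in the document.

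Target effect: 0.5 × 0.2 = 0.10 ASCOT units.

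Shift in an assisted survey: 0.1 × 0.2 = 0.02 to 0.2 × 0.2 = 0.04 units.

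Bias in the contrast = differential shift × share of surveys assisted.

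- All surveys assisted: 0.02/0.10 = 20% to 0.04/0.10 = 40% of the target.
- Share assisted 10% to 50% (assumption): 0.02 × 0.10 = 0.002 units, or 2%, up to 0.04 × 0.50 = 0.02 units, or 20%.

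If champions in both arms influenced answers equally and assisted equally often, the contrast would carry no bias from this source.

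**The case against.** The strongest reply is that this is a pragmatic cluster trial with self-reported outcomes. The article says openly that participants cannot be blinded, shows that both primary outcomes are questionnaires completed by participants, and lists champions' knowledge as a limitation. A careful reader can work out the position. That is largely fair, and it is why this is a correction to a description and not an objection to the design. The assessor-blinding claim still stands uncorrected beside those disclosures.

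Four stronger readings are tempting, and the document does not support them.

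- **That champions collect all older people's outcome data.** Collection is explicit only for control sites. Elsewhere their role is support where needed, and Recruitment offers reply-paid envelopes and text or email links that need no champion.
- **That no outcome is handled by any blinded person.** The article does not say who makes telephone calls or whether those entering data see the allocation. A journal article may leave this to the full protocol. The supportable statement is that no blinded assessor is described.
- **That the term single-blinded is false.** It can stand for the statistician alone.
- **That both co-primary outcomes are equally exposed.** The baseline KAMA precedes randomisation, a knowledge scale may be less open to response bias, and champions' stated part in provider surveys is to encourage and remind. The assisted-survey mechanism applies to the ASCOT.

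**Conclusion.** The point holds as an internal contradiction. The article claims blinded outcome assessors, while the follow-up scores for both co-primary outcomes come from participants it says cannot be blinded, and the named helpers and record abstractors know their arm. This conclusion rests on the text alone and needs no numerical assumption.

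The size of any resulting bias is unknown. A reader might take 20% to 40% of the target effect as an estimate. It is only an upper illustration, because it assumes a 0.1 to 0.2 SD shift, influence in one arm only, and every survey assisted. Smaller shares assisted, or similar influence in both arms, bring it down proportionately.

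The correction should be made because it changes what the trial can claim about detection bias. The design itself can stand.

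**What to change.** 1. In Group allocation, state that only the statistician is blinded, that participants and site champions are not, and that both primary outcomes are self-reported. Let single-blinded in the abstract refer to the statistician only.
2. In Limitations, extend the paragraph on champions' knowledge from recruitment to outcome assessment, covering help with the ASCOT and the abstraction of detection and referral data.
3. For each ASCOT survey, record the mode of completion and who, if anyone, assisted, and report both by arm. Any analysis by assistance should be labelled exploratory. Assistance is determined after randomisation and may depend on frailty and arm, so restricting to unassisted surveys can itself introduce selection.
4. If existing team members have no contact with sites or champions, they could give assisted or telephone follow-up. This cannot be presumed of the research team as a whole, which trains champions, contacts them every 2–3 weeks and visits each intervention site (Intervention; Process evaluation). If no such members are available, drop the assessor-blinding claim.

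Items 1 and 2 cost a wording amendment. Item 3 costs two short survey fields and a descriptive table; it can start during the trial, though surveys already returned may lack the information. Item 4 takes some staff time and is optional.

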### Data collection and management

For health providers, outcome questionnaires will take approximately 30–40 min to complete through the NARI-hosted REDCap database. For older people, questionnaires will take approximately 40 min. Outcomes will be entered into an electronic database by the research team and stored on a secure server. Participants will not be identifiable from any data that is published or otherwise publicly released. As the intervention is not a medical intervention, a data monitoring committee was not required by the Human Research Ethics Committee. Older adult participant data will be screened by site champions for any responses that indicate a concern requiring clinical follow-up (e.g. low mood) which will be undertaken by the site champion through their normal role as a senior social worker at the site, according to usual practice.

### Promoting retention and follow-up

Intervention and control sites will receive a gift hamper at each follow-up to encourage survey completion. Survey reminder notices will be distributed to all sites’ staff with a QR code for survey completion; at each of the three assessment points, those completing the survey will enter a draw for a $250 gift card. A poster benchmarking the site’s progress in survey completion against other sites (de-identified) and study promotion materials will also be placed in staff lunchrooms.

